#### Analyses

The effect of vitamin D supplementation compared to placebo will be determined using evaluation criteria, which are the changes in cognitive, functional and physical scores between W0 and W12 and between W0 and W24, using independent samples t-test or Mann-Whitney U test; and the between-group comparisons of changes in cognitive, functional and physical scores between W0 and W12, and between W0 and W24, using an analysis of covariance.

Any exploratory analyses here will use multivariate logistic and proportional hazards regression. In addition, the stratification criterion for randomization (i.e., the nature of dementia: AD or RD) will be also taken into account in the multivariate models. Excessive subgroup analyses can give rise to misleading results and therefore all subgroup investigations will be interpreted cautiously. In particular, subgroup analysis will be conducted depending on the severity of hypovitaminosis D at the beginning of the study (i.e., serum 25OHD concentration below or above 10 ng/mL) and on the severity of dementia at the beginning of the study (i.e., MMSE score below or above 15). Finally, special attention will be paid to participants that, while having hypovitaminosis D at the beginning, did not show high levels of PTH, to determine whether this group differentiates of the PTH responders in terms of therapeutic benefits.

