## Objectives

### Primary objective

The primary objective is to compare the effect after 24 weeks of the oral intake of vitamin D_3 _with the effect of a placebo on the evolution of cognitive performance in patients suffering from moderate ADRD and receiving memantine.

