## Methods

### Design

This is a unicentre, double-blind (with patient, carer, clinician, outcome assessor and investigators blinded), randomized, placebo-controlled, parallel group, intent-to-treat, superiority clinical trial. Figure 1 illustrates the trial design and Table 1 summarizes the timing of the trial. All participants receive trial interventions for 24 weeks as recommended by the European Medicines Agency (EMEA) guidelines [28]. The randomization is stratified depending on the nature of dementia (i.e., Alzheimer's disease [AD], or related disorders [RD]). Thus, for each stratum (2 strata), a distinct randomization list is established by the Clinical Research Centre (CRC) of Angers with the use of the N'Query randomization software. In order to best limit potential imbalances, a block randomization is used.

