### Assessments

Study assessment measures will be applied at baseline prior to randomization, at W12 and at W24. All measures in the study are already carried out systematically in every patient admitted to Angers University Memory Centre. Experience has shown that this mode of operation is feasible and appreciated by patients and their families, and has never caused a breakdown in care so far. For this reason, the large number of measures is not expected to exacerbate the loss to follow-up. To ensure adherence to the intervention, nurses are prescribed for all participants to administer medications safely and effectively. In addition, phone calls are planned to keep in touch with the participant and to recall the date of follow-up visits. Trial completion is defined as completion of 24 weeks on the trial medication or discontinuation of follow-up for any cause. Participants who discontinue taking the trial medications are encouraged to remain in follow-up. Arrangements for continued provision of the trial medication at the end of the trial is made on an individual basis thanks to a centralized serum 25OHD measurement at W24 which allows the investigating physician in charge of the patient making rapid and appropriate decisions regarding carrying on, modifying or discontinuing vitamin D supplementation at the end of the study.

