### Statistics

#### Sample Size Calculation

The trial aims to recruit 120 patients over a period of 52 weeks. According to previous literature, we estimate that the change in ADAS-cog score after 24 weeks in patients receiving memantine will be 1.25 ± 5 points on average [8]. In addition, it is usually considered in clinical trials among AD patients that the minimum clinically relevant change in ADAS-cog score is at least 3 points [40].

Thus, assuming a reference value of 1 and a variance of 25 (standard deviation estimated at 5), a two-sided test with an alpha risk of 5%, and a power (1 - beta) of 99%, the sample size to detect a 3-point difference in change from baseline in the ADAS-cog between the 'Intervention' group and the 'Placebo' group, is 52 subjects per group (total 104 subjects).

Taking into account the loss to follow-up (estimated at 15%), it is necessary to include a total of 120 subjects (60 per group). This sample size has also adequate power (i.e., 90%) to detect a smaller difference in ADAS-cog score (i.e., 2 points). The sample size calculation also assumes accounting for up to 12 covariables anticipating multivariate analyses, including the change in comorbid conditions possibly due to vitamin D supplementation [51] with subsequent indirect cognitive benefits (using the Cumulative Illness Rating Scale for Geriatrics [CIRS-G] score) [52], the education level [1], the season tested [16], and the serum concentrations of parathyroid hormone (PTH) and calcium [53].

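### As written, the primary W0–W24 comparison uses only patients with a W24 ADAS-cog; a repeated-measures model would let W12 scores inform it at almost no cost

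*Protocol article*

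**What the plan says.** The Design section describes the trial as "placebo-controlled, parallel group, intent-to-treat, superiority clinical trial". The time point that matters is fixed under Primary objective: "The primary objective is to compare the effect after 24 weeks of the oral intake of vitamin D_3". Comparison at 12 weeks is a secondary objective.

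Under Assessments, "Study assessment measures will be applied at baseline prior to randomization, at W12 and at W24", and Table 1 lists the ADAS-cog at both follow-up visits. The same section asks patients who stop trial medication to stay in follow-up. The Intervention group and Safety parameters sections take patients with hypercalcaemia out of the study.

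The Analyses section names two kinds of comparison. The first is of "changes in cognitive, functional and physical scores between W0 and W12 and between W0 and W24, using independent samples t-test" or the Mann-Whitney test. The second compares changes "between W0 and W12, and between W0 and W24, using an analysis of covariance". No repeated-measures model and no rule for missing scores is named, and the analysis set is not defined beyond the intent-to-treat label.

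The Sample Size Calculation section says: "Taking into account the loss to follow-up (estimated at 15%), it is necessary to include a total of 120 subjects (60 per group".

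**The concern.** A t-test, a Mann-Whitney test and an analysis of covariance of the W0–W24 change all need a W24 value. Unless something is added, a randomised patient without one has no outcome for the primary comparison. A W12 score from the same patient, already collected, plays no part in it.

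Completer means give the right treatment difference when loss is unrelated to outcome, or when the relation is the same in both arms and cancels. They do not when patients declining by W12 leave more often in one arm than in the other. The article gives no data on why patients leave. It does describe one exit that could be commoner in one arm, because it links hypercalcaemia to vitamin D. It gives no frequency for that event and no link between it and cognition.

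At stake is a modest bias in the main estimate, in a trial where a 3-point variation on the ADAS-cog is taken as clinically relevant.

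**Working it through.** **Inputs from the article.** 120 randomised, 60 per group; 15% loss; 3-point difference; SD of change 5; two-sided 5%; ADAS-cog at baseline, W12 and W24.

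**Assumptions (not in the article).** Correlation ρ between W12 and W24 change; the share of lost patients who have a W12 score; how loss depends on W12 change.

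**1. The plan's own loss figure.** 104 × 1.15 = 119.6, rounded up to 120, which is the stated total. Dividing instead gives 104/0.85 = 122.4, or 123. At 15% loss, 120 × 0.15 = 18 patients lack W24 and 102 remain, 51 per group. Separately from this point, the stated 52 per group for 99% power is reproduced only by a one-sample formula, (5 × (1.960 + 2.326)/3)² = 51.03, rounded up to 52. The two-sample formula gives 103 per group. The power figures below therefore start from the two-sample calculation.

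**2. What W12 scores add in precision.** For a likelihood-based estimate with n patients per arm having W24 and N having W12 or W24, the variance of an arm mean is SD² × [ρ²/N + (1 − ρ²)/n]. The effective size per arm is 1/[ρ²/N + (1 − ρ²)/n]. Power is Φ(3/(5√(2/n)) − 1.96).

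| Case | Effective n per arm | Power for 3 points |
|---|---|---|
| W24 completers only (n = 51) | 51.0 | 85.8% |
| Half of lost patients have W12 (N = 55.5), ρ = 0.5 | 52.1 | 86.5% |
| All lost patients have W12 (N = 60), ρ = 0.5 | 53.0 | 87.0% |
| All lost patients have W12 (N = 60), ρ = 0.8 | 56.4 | 89.0% |
| No lost patient has W12 | 51.0 | 85.8% |

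The largest gain is 89.0 − 85.8 = 3.2 percentage points.

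**3. What W12 scores add against bias.** Assume ρ = 0.6, W24 SD 5, a true difference of 3 points, and 15% lost after W12 in each arm. Let Z be the W12 change in SD units and let the log-odds of loss rise by 1 per SD.

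- An intercept of −2.05 gives 15% loss. Then E[Z × P(loss)] = 0.113, so the mean of Z among those who stay is −0.113/0.85 = −0.133.
- The W24 mean of completers in that arm shifts by ρ × SD × (−0.133) = 0.6 × 5 × (−0.133) = −0.40 points.
- This pattern in placebo only: completer difference 3 − 0.40 = 2.60. A simulation with 400,000 per arm (W12 SD 4) gives 2.61 for completers and 3.01 when W12 is used.
- Opposite patterns (log-odds +1 on placebo, −1 on vitamin D): 3 − 2 × 0.40 = 2.20 for completers, against about 3.0 using W12.
- Same pattern in both arms: the shifts cancel. The simulation gives 3.00 for completers and 2.99 using W12.

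**4. A check that needs no loss model.** If the between-arm difference among the 15% lost departs from that among completers by Δ points, the completer estimate is off by 0.15 × Δ. For Δ = 1 to 5 that is 0.15 to 0.75 points.

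**The case against.** The strongest reply is that this is a missing-data point in other words. The Analyses section names tests; it does not say that patients without W24 are excluded. A t-test or analysis of covariance can follow imputation, and that rule commonly sits in a full protocol or SAP, which is not shown. This stands, and the lack of a rule in the article is not counted as an error here.

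A reader might go further and infer that the article plans a completer analysis that contradicts its intent-to-treat label. The documents do not support that. Nothing departs from analysis by assigned arm, and patients who stop medication are asked to stay in follow-up, which fits the label. The 15% is a planning allowance to protect power. It does not define who is analysed, and an analysed number of 102 appears nowhere.

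A reader might also infer that W12 data are thrown away. They are not: they enter the separate W0–W12 comparison. They are unused only in the W24 comparison as written. Patients lost before W12 have no W12 score, so no model recovers them.

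The size of the bias rests on assumptions from outside the article. It vanishes when loss follows the same pattern in both arms, which is plausible under blinding. The illustrated shifts lie below the standard error at 51 per group, 5 × √(2/51) = 0.99, and in those scenarios they understate benefit. The estimate using W12 comes back to 3.0 because loss was made to depend only on W12 change. All of this stands and limits the point to an improvement.

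What the reply does not remove is that the named methods, followed literally, leave relevant and already collected data out of the primary comparison.

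**Conclusion.** The point holds in a limited form. As written, the primary W0–W24 comparison uses only patients with a W24 ADAS-cog, and W12 scores of patients lost after W12 do not inform it, in a trial labelled intent-to-treat that plans for about 15% loss.

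The benefit of a change is mainly protection against bias: about 0.4 to 0.8 of a 3-point effect if loss related to W12 decline differs between arms, and none if it does not. These figures assume a W24 SD of 5, a correlation of 0.6, all loss after W12 and log-odds of ±1 per SD. The gain in power is at most about 3 percentage points over the assumed range, and zero if no lost patient has a W12 score. It is worth doing because it is cheap, not because the plan has been shown to be wrong.

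**What to change.** State the primary analysis as a mixed model for repeated measures on ADAS-cog change at W12 and W24. Include treatment, visit, treatment-by-visit, baseline ADAS-cog, baseline-by-visit and AD/RD stratum, with an unstructured covariance over the two visits. Analyse patients in their assigned arm, including every randomised patient with at least one post-baseline ADAS-cog. The W24 treatment contrast is primary; the W12 contrast from the same model serves the 12-week cognitive secondary objective. Keep the W24 analysis of covariance in completers as a sensitivity analysis.

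The cost is a change of wording, slightly more modelling and no extra data. The article lists the trial as recruiting, so the change can be made before unblinding. The price in assumptions is missing at random: loss may depend on baseline and W12 scores but, given those, not on the unseen W24 score. That is weaker than what the completer comparison needs, but it is still an assumption and should be stated.

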**Methods:**

The AD-IDEA Trial is a unicentre, double-blind, randomized, placebo-controlled, intent-to-treat, superiority trial. Patients aged 60 years and older presenting with moderate ADRD (i.e., Mini-Mental State Examination [MMSE] score between 10-20), hypovitaminosis D (i.e., serum 25-hydroxyvitamin D [25OHD] < 30 ng/mL), normocalcemia (i.e., serum calcium < 2.65 mmol/L) and receiving no antidementia treatment at time of inclusion are being recruited. All participants receive memantine 20 mg once daily -titrated in 5 mg increments over 4 weeks- and each one is randomized to one of the two treatment options: either cholecalciferol (one 100,000 IU drinking vial every 4 weeks) or placebo (administered at the same pace). One hundred and twenty participants are being recruited and treatment continues for 24 weeks. Primary outcome measure is change in cognitive performance using Alzheimer's Disease Assessment Scale-cognition score. Secondary outcomes are changes in other cognitive scores (MMSE, Frontal Assessment Battery, Trail Making Test parts A and B), change in functional performance (Activities of Daily Living scale, and 4-item Instrumental Activities of Daily Living scale), posture and gait (Timed Up & Go, Five Time Sit-to-Stand, spatio-temporal analysis of walking), as well as the between-groups comparison of compliance to treatment and tolerance. These outcomes are assessed at baseline, 12 and 24 weeks, together with the serum concentrations of 25OHD, calcium and parathyroid hormone.

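### An unadjusted test and an ANCOVA are both planned for the 24-week ADAS-cog change and neither is named as primary; one ANCOVA with baseline and stratum should decide

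*Protocol article*

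**What the plan says.** The abstract fixes the endpoint: "Primary outcome measure is change in cognitive performance using Alzheimer's Disease Assessment Scale-cognition score". The primary objective sets the time point at 24 weeks.

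The Analyses section covers all cognitive, functional and physical change scores, W0–W12 and W0–W24, in one sentence. The effect of vitamin D is to be determined "using independent samples t-test or Mann-Whitney U test; and the between-group comparisons of changes in cognitive, functional and physical scores", and the second half of the sentence ends "between W0 and W24, using an analysis of covariance". The ANCOVA covariates are not listed there.

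On the stratum, the Design section says "The randomization is stratified depending on the nature of dementia", with AD and related disorders as the two strata. In the Analyses section the stratum "will be also taken into account in the multivariate models". That sentence follows one on exploratory logistic and proportional hazards regression.

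The Sample Size Calculation section uses "a two-sided test with an alpha risk of 5%, and a power (1 - beta) of 99"%. It also anticipates up to 12 covariables in multivariate analyses. Those it names are change in comorbidity (CIRS-G), education, season, PTH and calcium. The list is not presented as complete, and baseline ADAS-cog is not among those named.

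**The concern.** Two analyses of one primary endpoint, joined by 'and' with no ranking, leave the deciding result open. If they disagree at the 5% level, the text does not say whether the trial has succeeded. A choice made after seeing the results would no longer be a 5% test.

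The two analyses also differ in what they use. The t-test and the Mann-Whitney test take the change score as it stands: they do not condition on baseline ADAS-cog, and they do not reflect the AD/RD stratification. An ANCOVA can do both with data the trial already collects. The t-test and Mann-Whitney also address different quantities, means in one case and ranks in the other.

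**Working it through.** **1. Inputs.** From the Sample Size Calculation section: "a variance of 25 (standard deviation estimated at 5"), the aim "to detect a 3-point difference in change from baseline in the ADAS-cog", two-sided 5%, 52 evaluable per group. Assumed, because the document gives no value: a correlation r between baseline ADAS-cog and its change of 0 to −0.5. Some runs add a 70:30 AD:RD split and a stratum–change correlation of 0.2, also assumed. Changes are simulated as normal.

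**2. The plan's own figure.** n per group = 2 × 25 × (1.960 + 2.326)² / 3² ≈ 102.1, so 103 for 99% power, not 52. With 52 per group, SE = 5 × √(2/52) = 0.981 and power = Φ(3/0.981 − 1.960) = Φ(1.10) = 86.4%. The stated figure does not reproduce. That is a separate defect. Here it only sets the starting power for step 4.

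**3. Type I error.** Each test alone stays near 5% (simulated 4.6–5.3%). The tests are strongly correlated: for t-test and baseline-adjusted ANCOVA the correlation is about √(1 − r²), which is 0.95 at r = −0.3 and 0.87 at r = −0.5. So picking the significant result inflates the error only moderately. Simulated rates, 52 per group (10,000 or 20,000 null trials per setting; ranges are across separate runs):

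| Assumed r | Either of: unadjusted test (t, or Mann-Whitney if normality is rejected) and ANCOVA | Any of t-test, Mann-Whitney, ANCOVA |
|---|---|---|
| 0 | 5.5% | 6.1–6.4% |
| −0.2 | 6.2% | 6.4–6.9% |
| −0.3 | 6.4% | 6.7–7.1% |
| −0.5 | 7.1% | 7.7–8.1% |

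The Monte Carlo standard error at 8.1% with 10,000 trials is √(0.081 × 0.919/10,000) = 0.27 points, so two standard errors reach 8.6%. Rounded outwards: 5–8% for two analyses, 6–9% for three.

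**4. Power for a true 3-point difference.** ANCOVA reduces the SD to about 5 × √(1 − r²). At r = −0.3 this is 4.77, SE = 4.77 × √(2/52) = 0.935, and power = Φ(3/0.935 − 1.960) = 89.4%. At r = −0.5 it is 4.33, SE = 0.849, and power = 94.2%.

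| Assumed r | t-test, simulated | ANCOVA, simulated | ANCOVA, approximation |
|---|---|---|---|
| 0 | 86% | 86% | 86.4% |
| −0.2 | 84.7% | 85.3% | 87.7% |
| −0.3 | 86.1% | 88.2% | 89.4% |
| −0.5 | 85.6% | 93.6% | 94.2% |

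The t-test's power does not depend on r, so its spread (84.7–86.1%) is Monte Carlo noise. Within the same simulated data the gain is 0.6 points at −0.2, 2.1 at −0.3 and 8.0 at −0.5. With the stratum effect of 0.2 added, the gains are about 3 points (87% to 90%) at −0.3 and 9 points (86% to 95%) at −0.5.

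**5. Disagreement.** With a true 3-point difference, the three tests do not all agree on significance in about 5%, 8% and 13% of trials at r = 0, −0.3 and −0.5 (the last two with the stratum effect).

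**The case against.** The best defence is that an unadjusted comparison followed by an adjusted one is a common reporting sequence. 'Or' between t-test and Mann-Whitney most naturally means one test chosen by distribution. A reader might infer three competing tests, any of which may carry the claim, and conclude that the 5% error does not hold. The text does not support that: it contains no any-of-three rule, and the inflation arises only if results are selected after the fact.

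The stratum may also be handled already. A reader might infer that it is confined to the exploratory logistic and hazards models. But the sentence is worded as an addition, and the covariables are discussed within an ADAS-cog sample-size calculation, so the ANCOVA may be one of the models meant. The text does not settle it.

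The unadjusted tests are not invalid either. They use change from baseline, and leaving out a stratification factor generally makes a test conservative.

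Finally, the rule for choosing between t-test and Mann-Whitney, and the full covariate list, are details that an article may leave to an analysis plan that is not shown here.

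All of this stands, and it limits the point. It does not answer the remaining defect: the article itself sets two analyses of the primary endpoint side by side and ranks neither.

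**Conclusion.** The point holds in this limited form. The text names an unadjusted test and an ANCOVA for the same W0–W24 ADAS-cog change and designates neither as primary. The unadjusted test conditions on neither baseline nor stratum, and whether the ANCOVA includes the stratum is unclear.

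Confidence is high on the text and lower on the size. The error inflation is modest and conditional on selection. The power gain is worthwhile only if baseline and change are correlated at about −0.3 or more strongly. All sizes rest on normal changes, SD 5, 52 per group and a correlation that the document does not give.

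The shortfall of 86% against the stated 99% should not be used to enlarge this point: it comes from the sample-size formula. ANCOVA does not close it, since even at −0.5 power is about 94% and 99% would need 77 per group.

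**What to change.** State in the protocol or analysis plan, before unblinding, that the sole primary test is an ANCOVA of ADAS-cog change W0–W24 on treatment, with baseline ADAS-cog (continuous) and AD/RD stratum as covariates, two-sided 5%. Report the t-test or Mann-Whitney only as labelled sensitivity analyses. Use the same model, with each outcome's own baseline score and the stratum, for the other continuous outcomes. Keep post-randomisation variables, such as the change in CIRS-G, out of the primary model.

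The cost is one or two sentences. No new data are needed: the method is already named, and baseline score and stratum are already recorded. The sample-size calculation needs its own correction.

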### Ethical considerations

The protocol received Angers Research Ethics Committee approval, and was approved by the AFSSAPS (French health products safety agency). The trial is conducted in compliance with the European Union Clinical Trials Directive (2001/20/EC), the French National Commission for Information Technology and Freedom (1978), the Public Health Code of Ethics, the International Conference on Harmonization guidelines for Good Clinical Practice (CPMP/ICH/135/95), the principles of the Declaration of Helsinki (1996) and other requirements as appropriate.

An Independent Data Monitoring Committee (IDMC) will monitor the progress of the trial including: recruitment, protocol adherence, serious adverse events and side effects of treatment as well as the difference between the trial treatments on the primary outcome measures. The IDMC will produce a report to the Trial Steering Committee (TSC) after every meeting and can recommend premature closure of the trial following clear evidence of benefit or harm in accordance with the IDMC charter.

The main ethical issue here is related to the delay of vitamin D supplementation in the 'Placebo' group. This treatment delay of 24 weeks seems yet acceptable since vitamin D supplementation has not yet proved efficient for ADRD patients. Due to this reasonable doubt and to the lack of standard treatments to be associated with memantine, resorting to a placebo is thus conceivable and justifies the study.

In addition, subject participating in this research can also expect personal benefits. Individual expected benefits are:

- All included subjects receive memantine, a standard antidementia treatment that is appropriate for moderate ADRD.

- For subjects within the 'Intervention' group, the treatment will correct the hypovitaminosis D.

- Since presenting with hypovitaminosis D is an inclusion criterion, participating in this study constitutes an opportunity even for subjects receiving a placebo. Indeed, in the hypothesis of an effectiveness of vitamin D, the subjects in the 'Placebo' group would undergo a potential transient loss of opportunity (i.e., being deficient and receiving a placebo during the study period) balanced by permanent growing opportunities at the end of the study (i.e., receiving vitamin D supplementation).

- The expected benefits for the 'Intervention' group are potentially important because, in the hypothesis of an efficient action of the combination of memantine plus vitamin D on brain, participation in this research may prevent cognitive decline and improve ADRD symptoms.

The expected collective benefits for this research are an improvement of the knowledge of the non-skeletal effects of vitamin D, and in particular of the cognitive effects of the combination of vitamin D plus memantine.

